#### Relatives

At T3, the first, second and third-degree relatives are invited by the counselee to complete a single questionnaire. Eligible relatives are at increased risk (that is, eligible for genetic testing and/or regular surveillance), are aged ≥18 years, and able to read and write Dutch.

### Recruitment and informed consent

#### Counselees

In the Netherlands, it is considered standard care for the Clinical Genetics department to send counselees a summary letter after the last counseling session; this letter reaffirms the information provided and aims to facilitate the communication process in the family. When this letter has been received, clinical geneticists and counselors will invite eligible counselees to participate using an information letter, an informed consent form, a return slip to decline participation, and an invitation to complete a (web-based) questionnaire (T1).

We will use a two-stage randomization and a consent procedure with consent to postponed information [34-36]. In this procedure, counselees are masked for the exact study objective. However, they are informed that: 1) the study aims to assess issues pertaining to family disclosure, 2) the study has an additional purpose, and 3) a letter with the postponed information about the additional research question and reasons for not informing them during recruitment will be sent after the study. Postponed information enables a blind design and avoids a less favorable outcome in the control group resulting from their knowledge that the other counselees receive extra care. This procedure has been used previously and resulted in no major objections [35-38].

In case of consent, counselees will be asked to complete a web-based baseline questionnaire (if preferred, a paper version of the questionnaire is available). Counselees will then be randomized (Figure 1). Counselees in the intervention group will receive an information letter about the additional counseling, an informed consent form for the intervention, and a return slip to decline participation. Within one week they will be contacted by telephone to provide them with additional information about the intervention and are asked for their consent. Counselees in the control group will receive no additional information. Information about the randomization procedure will be included in the debriefing letter for counselees, which is sent after the study.

#### Relatives

In the Netherlands, medical-ethical regulations preclude counselors/researchers from directly approaching a counselee’s relatives. Therefore, at T3 all counselees will be asked to inform their relatives about the study. In case of consent, counselees will receive more detailed information and the family pedigree will be used to decide which individuals are eligible for study inclusion. Then, counselees will be asked to invite (by mail) their eligible first, second and third-degree relatives to participate in the study. For this, they can use an introductory letter, a questionnaire and a return envelope, which are made available by the researchers. Relatives willing to participate complete the questionnaire, thereby giving their consent, and return the questionnaire to the researchers. Researchers do not collect the full names/addresses of the relatives but assign a study ID number to each relative. In case of nonresponse, counselees will be asked to send their relatives a reminder after three weeks.

### Control group

Counselees in the control group will receive standard care only. It is recommended by the Dutch Society for Clinical Genetics that, during the first consultation, counselees are informed about the possible consequences of genetic testing for their relatives [5]. If the genetic counseling result is relevant for relatives, counselees are asked to inform their at-risk relatives. After the last counseling session, counselees receive a summary letter which reaffirms the information provided during the counseling. In case of hereditary cancer, a separate family letter is provided about the test results and recommendations for surveillance measures for the counselees and their relatives. In the Netherlands, although all departments of Genetics consider providing these letters as part of standard care, no specific guidelines are available; this implies that some differences may exist between these letters.

### Intervention group

Counselees in the intervention group will receive an additional counseling session provided by psychosocial workers specialized in genetics, aimed at supporting them to inform their at-risk relatives. The intervention will be delivered by telephone. The rationale for this method is that: 1) this allows for contact with counselees with limited knowledge/motivation to inform relatives and who are therefore unlikely to visit the department for additional counseling, 2) a telephone intervention is more likely to be implemented in daily care, and 3) a telephone-based intervention was earlier found to be effective in increasing the number of relatives that attended genetic services [32].

We developed a five-step model for the additional counseling session [39] (Table 1) based, in part, on the work of Rollnick *et al*. [40]. Their directive client-centered counseling style, known as Motivational Interviewing (MI), elicits behavior change by helping clients to explore and resolve ambivalence [40]. MI is guided by the following principles: expressing empathy by use of reflective listening, developing discrepancy between goals and current behavior, assuming that clients are responsible for the decision to act or not, rolling with resistance rather than confronting, and supporting self-efficacy.

**Table 1 T1:** Intervention elements

**Phase 1: exploring**		
Step 1	Agenda setting	Introducing the subject of family communication about hereditary or familial cancer risks and preventive measures. Explicitly ask the counselee if he/she is willing to discuss this issue.
Step 2	Exploring	Systematically exploring counselees’ current and planned pattern of informing relatives. Psychosocial workers investigate whether the counselee correctly knows which family members are at risk and which information should be provided to them.
*Evaluation*		*After the first phase the psychosocial worker verifies whether or not all at-risk relatives are informed thoroughly (thoroughly = at least the written advice in the summary letter). If the counselee has informed all at-risk relatives properly the psychosocial worker will end the counseling session. If not, the psychosocial worker will start phase 2.*
**Phase 2: additional information and brainstorming**		
Step 3	Additional information	Additional or corrective information is provided, if needed. For example, in case of BRCA 1/2 it is important to stress that male relatives can also transmit the risk and thus need to be informed.
Step 4	Building motivation	The purpose of the fourth phase is to build motivation and strengthen self-efficacy. Psychosocial workers invite counselees to verbalize arguments in favor of informing relatives, to reinforce these arguments and thus strengthen the counselees’ motivation. Any barriers are also assessed and discussed. These barriers can be practical, for example, not having personal contact, and/or emotional, for example, causing too much distress. Also, reasons for (non)disclosure are explored, so as to understand the counselee’s perspective and motives, to build rapport and reduce resistance. Likewise, the counselees’ confidence in their ability to correctly and sufficiently inform relatives is assessed and strengthened.
Step 5	Brainstorming	During the final phase, the psychosocial worker invites the counselee to engage in active brainstorming on possible solutions for informing more difficult to approach relatives. The goal is to develop a plan for informing these relatives.

The intervention is delivered by one of five psychosocial workers. All will have attended two days of training days provided by two trainers from the department of Medical Psychology (AMC) who have extensive experience with MI. These sessions provide more information about MI and the intervention. Moreover, interviewing techniques are practiced with a trained actor and individual feedback is provided by the trainers.

As the psychosocial workers have access to counselees’ medical files and also have their pedigree available they are well informed; this avoids counselees having to discuss their situation/issues again. Counselees are informed about this procedure as part of the informed consent procedure.

Details on the development of the actual intervention will be published separately.

### Quality of the intervention

All intervention sessions will be audio-recorded to: examine whether the psychosocial workers perform their task according to the intervention protocol, trace differences between the psychosocial workers, and monitor changes in intervention delivery over time.

All recordings will be divided into four sets of 33 consecutive sessions. From each set 12 recordings will be chosen, stratified by psychosocial worker, and analyzed to investigate whether psychosocial workers correctly follow the steps of the intervention (Table 1). Scoring of the 48 recordings will be based on an adapted version of an instrument developed earlier [41].

### Primary outcome measures

At T2 the primary outcomes will be assessed by questionnaire (and partly by telephone) using specific instruments (Figure 1). Details on the development and psychometric properties of the outcome measures will be published separately.

Knowledge will comprise counselees’:

1. Insight into which relatives need to be informed, as indicated by a percentage ‘correct knowledge’ specifying the relative number of family members that need to be informed, correctly remembered by the counselee (range 0 to 100).

2. Knowledge about surveillance measures for relatives, as indicated by the percentage ‘correct knowledge about surveillance options’ that indicates how many screening options for relatives (1 to 6), are correctly remembered by the counselee (range 0 to 100).

3. Risk perception, as measured with two items: perceived lifetime breast and/or ovarian or colon cancer risk in percentages, and perceived breast and/or ovarian or colon cancer risk as compared with the average Dutch woman or person (5-point Likert scale: 1 = very strongly lowered, 5 = very strongly heightened).

4. General knowledge about hereditary breast or colon cancer, which includes six items developed by Pieterse *et al*. [42] based on the work of Claes *et al*. [14]. All items are presented as statements with three response categories (‘Correct’, ‘Incorrect’, or ‘I do not know’). A higher score indicates more knowledge about hereditary cancer.

#### Motivation

Counselees’ motivation to inform relatives will be assessed using a 30-item instrument based on a 36-item questionnaire developed by Finlay *et al*. [43]. All items are potential determinants of disclosure of information to relatives and are answered on a 5-point Likert scale (1 = plays no role in disclosure, 5 = plays a large role in disclosure). Items will be presented to participants as: ‘Reasons to inform relatives’ (positive motivation, 13 items) and ‘Reasons for not informing relatives’ (negative motivation, 17 items). For each scale a total score is created, with a higher score indicating more positive or negative motivation to inform relatives (range 13 to 65 and 17 to 85, respectively).

#### Self-efficacy

Self-efficacy is the measure of one’s own ability to complete tasks and reach goals [44]. Index patients will be asked to indicate how sure they are that they are able to overcome seven obstacles in informing relatives, on a 4-point Likert scale (1 = not sure at all, 4 = very sure). A total score is created, with a higher score indicating more self-efficacy (range 7 to 28).

### Secondary outcome measures

Secondary outcome measures include the following:

1. Relatives’ knowledge, which will be assessed using the same instruments as used by counselees, comprising knowledge about surveillance, risk perception and general knowledge about hereditary breast and/or ovarian cancer or colon cancer.

2. Relatives’ intention to engage in genetic counseling, testing and/or preventive measures, measured with six items using the following format ‘How likely is it that you will have a colonoscopy in the coming year?’ Items are scored as 1 = very unlikely, to 5 = very likely [45].

3. Relatives’ evaluation of the way they have been informed, which includes seven items about the way relatives are informed and their evaluation of the communication process. Items were developed for the purpose of this study and are based on those developed by Vos *et al*. [46].

4. Counselees’ evaluation of the intervention, which includes 18 questions about the intervention and its content, psychosocial workers’ performance, and practical issues related to the intervention (for example, right moment in time, intervention conducted by telephone).

5. Psychosocial workers’ evaluation of the intervention, in which psychosocial workers are asked to complete ten items after each additional counseling session to evaluate the intervention. The aim is to gain insight into their experiences with the intervention, to identify issues to improve the intervention, and to track (in) congruence between counselees’ and psychosocial workers’ experiences with the intervention.

### Counselees’ characteristics

Counselees’ characteristics include the following:

1. Demographic variables, which include age, gender, educational level, age of their children, and marital status.

2. Clinical characteristics, comprising genetic test result, cancer diagnosis, number of relatives to be informed, number of informed relatives (as reported by the counselee), age at which the counselee was first confronted with cancer in the family, and types of cancer in the family.

### Sample size

For the primary research question we aim for a medium effect size. At baseline (T1), we assume no differences in primary outcomes between the intervention and control group. At T2 we expect to find a medium effect size. We assume this to be 0.5 for the intervention group and 0.2 for the control group, taking into account that the outcomes in the control group may be slightly affected by that fact that they are aware that the study focuses on informing their relatives; this effect is estimated to last until follow-up (T3).

Based on these assumptions, we require 132 patients in each group to have 80% power to detect an intervention effect (group/time interaction) that is significant at the 0.05 level (assuming a 0.7 correlation between measurements). In addition, we have a 99% chance to detect differences between measurement moments and a 46% chance to detect group differences overall.

Assuming a response rate of 50% and a 20% dropout, we need to approach 660 counselees. Preliminary work has shown that counselees are advised to inform (on average) 4.6 at-risk relatives. Assuming that counselees provide contact information for (on average) two relatives and that 50% of these relatives will complete the questionnaire, it is estimated that we will have data on 264 relatives.

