**Methods/Design:**

A multicenter randomized controlled trial with parallel group design will be used to compare the effects of an additional telephone counseling session performed by psychosocial workers to enhance the disclosure of genetic cancer information to at-risk relatives (intervention group) with a control group of standard care. Consecutive index patients with relatives at risk for hereditary or familial breast and/or ovarian cancer or colon cancer, are randomly assigned (block size: 8; 1:1 allocation ratio) to the intervention (n = 132) or control group (n = 132, standard care). Primary outcomes are counselees’ knowledge, motivation and self-efficacy regarding informing their relatives.

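### 132 per arm is the number left after 20% dropout in the sample-size section but the number randomised in the abstract; the implied 330 to randomise is never stated

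*Protocol article*

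**What the plan says.** The figure of 132 per arm does two jobs in the protocol article.

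- **Sample size section, power statement:** "we require 132 patients in each group to have 80% power to detect an intervention effect (group/time interaction"), an effect "that is significant at the 0.05 level (assuming a 0.7 correlation between measurements"). The inputs are no difference at T1, a change of 0.5 in the intervention arm and 0.2 in the control arm at T2, and persistence to T3. The section also states 99% power for time and 46% for the overall group difference.
- **Sample size section, recruitment:** "Assuming a response rate of 50% and a 20% dropout, we need to approach 660 counselees".
- **Sample size section, relatives:** two relatives per counselee and 50% completion are taken to give data on 264 relatives.
- **Abstract, Methods/Design:** index patients are randomly assigned "to the intervention (n = 132) or control group (n = 132, standard care").

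The article gives neither 330 nor 165 per arm as a number to randomise.

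**The concern.** The recruitment arithmetic treats 264 as the counselees who still provide data after dropout. The abstract treats the same 264 as those allocated. Under the plan's own 20% dropout both cannot be true, because randomising 264 leaves about 211.

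The difference matters because recruitment is in progress (Trial status) and this number tells the team when to stop. A team working from the abstract would stop 66 counselees short of what the sample-size section implies. The trial would then have less than its stated power for the primary hypothesis, and fewer relatives for Hypothesis 2.

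**Working it through.** **1. Recruitment arithmetic (inputs from the Sample size section; no model needed)**

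- 264/(0.5 × 0.8) = 660, the stated figure.
- Forward: 660 × 0.5 = 330 enter; 330 × 0.8 = 264 remain.
- If 264 already contained the dropout allowance, 264/0.5 = 528 approached would be enough.
- Relatives: 264 × 2 × 0.5 = 264. Relatives are invited only at T3, so this also needs 264 counselees still taking part at T3.

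Within that section, then, 264 is the number after dropout.

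**2. Reproducing the stated power**

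Stated inputs: "At baseline (T1), we assume no differences in primary outcomes between the intervention and control group"; "We assume this to be 0.5 for the intervention group and 0.2 for the control group"; "this effect is estimated to last until follow-up (T3"). The between-arm differences are therefore 0, 0.3, 0.3 SD at T1, T2, T3. Alpha is 0.05 and the correlation is 0.7. My assumptions, which the article does not state, are first-order autoregressive correlation (0.7 between adjacent waves, 0.49 between T1 and T3), SD 1, and a Geisser-Greenhouse-corrected repeated-measures F test.

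- Sum of squared deviations of (0, 0.3, 0.3) about their mean of 0.2: 0.04 + 0.01 + 0.01 = 0.06.
- The variances of the two orthonormal time contrasts are 0.51 and 0.23, with mean 0.37.
- ε = (0.51 + 0.23)²/[2(0.51² + 0.23²)] = 0.5476/0.626 = 0.875.
- Noncentrality = (132/2) × 0.06/0.37 = 10.70. Multiplied by ε, with degrees of freedom 2ε and 2ε × 262, power is **80.2%** (131 per arm gives 79.9%).
- Group effect: mean difference 0.2; variance of the three-wave mean (3 + 4 × 0.7 + 2 × 0.49)/9 = 0.753; noncentrality 66 × 0.04/0.753 = 3.50; power **46.2%**.
- Time effect: above 99%.

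One model returns all three stated figures at 132 complete per arm. The alternatives fit worse:

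| Model, 132 per arm | Interaction | Group |
|---|---|---|
| Stated in the article | 80% | 46% |
| Autoregressive 0.7, corrected F | 80.2% | 46.2% |
| Autoregressive 0.7, multivariate test | 81.6% | 46.2% |
| Equal correlation 0.7 | 91.1% | 44.0% |
| T1–T2 change score only | 88.2% | about 26% |

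On the model that fits, 132 contains no dropout allowance.

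**3. If only 264 are randomised and 20% drop out**

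264 × 0.8 = 211, or 105.6 per arm.

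*Completers only:*
- Noncentrality (105.6/2) × 0.06/0.37 = 8.56; power **70.3%** (multivariate test 71.7%).
- Check that does not need the correlation structure, scaling the stated 80% by a normal approximation: Φ(2.80 × √0.8 − 1.96) = 70.7%.

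*Three-wave likelihood model keeping partial data* (132 per arm randomised, all with T1; same autoregressive correlation; multivariate test, 81.6% with complete data):

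| When the 20% leave | Interaction power |
|---|---|
| All after T2 | about 81% |
| Half before T2, half after | about 78% |
| All before T2 | about 74% |

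*Imputation from control data:* if the 20% lost from the intervention arm take control values, the difference shrinks to 0.3 × 0.8 = 0.24. Scaling the stated 80% gives Φ(2.80 × 0.8 − 1.96) = 61%.

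*Relatives:* 211 × 2 × 0.5 = 211.

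**The case against.** **The sample-size section already allows for dropout, and the conflicting figure stands in a condensed abstract.** This is true, and on that section's reading the stated 80% holds. The Randomization section sets no number at which allocation closes, so a shortfall is conditional on the abstract being followed. But the abstract is the only place that gives a number to randomise, so the conflict needs settling.

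**A reader might infer that power is simply 70%, not 80%.** The documents do not support that as a flat statement. It is a completers-only figure. T1 is completed before randomisation, and the planned multilevel analysis nests three waves within counselees, so partial data can recover much of the loss. The correlation structure is also inferred: with equal correlation of 0.7 among all waves, completers alone would give about 83%, although that structure does not return the stated 80% at 132. A range with its assumptions is what can be defended.

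**Imputation keeps 132 per arm in the analysis.** It does so nominally, but filling in from control data adds no information and pulls the arms together, so it does not restore 80%.

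**The 20% might be lost before randomisation.** Then 660 approached and 264 randomised would agree, and the article does not say outright when dropout occurs. The reading is strained, though. Randomisation follows consent and the T1 questionnaire, and Data analysis links dropout to incomplete data that will be imputed, which points to loss after entry.

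**A reader might take the planned recordings ("All recordings will be divided into four sets of 33 consecutive sessions", so 132) as further evidence that 264 means counselees retained.** They are not. Sessions follow soon after randomisation and before most follow-up loss, so 132 sessions fit 132 randomised to the intervention at least as well.

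**Conclusion.** The inconsistency is real and needs no model to show. The sample-size arithmetic makes 264 the number after dropout and 330 the number randomised; the abstract makes 264 the number randomised.

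Its consequence is conditional. If 330 are randomised, the stated 80% and the 264 relatives stand, and only the abstract is wrong. If 264 are randomised, interaction power is about 70% on completers, or roughly 74% to 81% with partial data used, against 80% to 82% with complete data on 132 per arm; expected relatives are about 211. These power figures rest on autoregressive correlation of 0.7, inferred because it returns the stated 80% and 46% together, and on the 20% being lost after randomisation. Control-based imputation could lower power further.

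**What to change.** State one number, and say whether it is randomised or retained.

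- **Either** correct the abstract and the randomisation target to 330 (165 per arm), with 132 per arm expected to provide data after 20% dropout. The planned 660 approached already yields this, so no recruitment beyond the plan is needed.
- **Or** keep 264 randomised and restate the interaction power as about 70% on completers, giving the correlation structure and dropout assumptions (with the partial-data range if that analysis is intended), and restate the expected relatives as about 211.

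The cost is a rewording of the abstract and the sample-size text, plus a check that the recruitment target given to the centres and the randomisation system matches.
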